### Intervention

The intervention and data collection take place at the CHIP or on the downtown campus of McGill University. The GLB (in its standard or enriched form) will be delivered over one year (12 weekly core sessions, 4 transitional sessions over 3 months, and 6 monthly support sessions). Group sizes will comprise of approximately 6-10 individuals and the sessions will last for approximately one hour. Groups are led by trained lifestyle coaches. The lifestyle coaches are doctoral students in clinical health psychology and have completed the GLB 2-day training workshop at the University of Pittsburgh. The lifestyle coaches will have continuous support on as-needed basis from the Diabetes Prevention Support Center (DPSC) of the University of Pittsburgh.

The enriched GLB group will receive the exact same intervention with instructions for if-then planning and mental practice integrated into the intervention manual. Instructions for delivering if-then planning and mental practice are based on our previous studies [23-25]. Specifically, the concepts of if-then planning and mental practice are introduced to participants in Session 1 and practiced with the example of weighing oneself and tracking one’s food intake (see example in Additional file 1). Lifestyle coaches will guide participants through the formation of effective if-then plans using structured if-then plan handouts (see Additional file 2 for an example). The intervention manual and handouts are available from the authors.

### Compensation for participation and assessments

There will be no financial compensation for participating. Participants do not have to pay for the program. They will receive all program materials (pedometer, handouts, etc.) for free.

### Outcome measures

Measures assessed in the study are reported in Table 1 and described below. The *primary outcome for Aim 1* will be the mean difference in percent body weight loss between the enriched and the standard GLB at 3, 12, and 24 months. Weight loss was chosen as the primary outcome because it was the most important predictor of diabetes incidence in the large-scale diabetes prevention studies [9-11]. Diabetes incidence was reduced by 16% for every kg of weight loss in the original DPP [20]. Weight is assessed with a digital scale without shoes to the nearest 0.1 kg.

**Table 1 T1:** Measures

**Outcomes**	**Variable**	**Measure/source**
**Primary outcome (Aim 1)**	**Mean difference in % body weight loss**	- Weight In Kg (Digital Scale)
**Secondary outcomes (Aim 1)**	**(1) Goal achievement**	
	a. % reaching weight loss goal	- Weight In Kg (Digital Scale)
	b. % reaching exercise goal	- Sum of min. over 7 days (tracking sheets)
	**(2) Diabetes risk factors**	
	a. Waist circumference	- Tape (cm)
	b. Hemoglobin A1c	- Immuno assay
	c. Blood pressure	- Mercury sphygmomanometer
	d. Total cholesterol/HDL ratio	- Enzymatic assay
	**(3) Physical activity**	
	a. Total duration	- Minutes (online tracking)
	b. Steps taken	- Pedometers (online tracking)
	c. Metabolic equivalents	- Ainsworth tables
	d. Aerobic fitness	- EST (test duration in minutes)
**Aims 2 and 3**	**Habit formation indices:**	
	**(1) Self-monitoring index**	
	a. Weight	- Days per week (0-7, online tracking)
	b. Fat grams	- Days per week (0-7, online tracking)
	c. Calories	- Days per week (0-7, online tracking)
	d. Physical activity	- Days per week (0-7, online tracking)
	**(2) Behavior change index**	
	a. Fat grams intake	- Daily average (online tracking)
	b. Calorie intake	- Daily average (online tracking)
	**(3) Habit strength index**	- Self-report index of habit strength
	a. Self-monitoring	
	b. Behaviors	
**Moderators**	**Socio-demographic variables**	- Self-report questionnaire
	Age, gender, ethnicity, education, socio-economic status, smoking status	

### Secondary outcome measures for Aim 1

Table 1 outlines the secondary outcome measures for Aim 1, which are: (1) Goal achievement of (a) the weight loss goal (7% of body weight) and (b) physical activity goal (150 min/week) at 3, 12, and 24 months; (2) measures of other health relevant outcomes measured at 3, 12, and 24 months, compared to baseline levels; and (3) physical activity and aerobic fitness assessed using 4 methods to capture different aspects of physical activity and aerobic fitness, namely: (a) how many minutes of physical activity participants engaged in during the day (online tracking), (b) the number of steps taken during the day recorded using a pedometer, and (c) the metabolic equivalents (MET) of the different physical activities over 7 days translated into step equivalents using the tables developed by Ainsworth [46]. Participants will track their weight changes and physical activities online through CHIP’s myhealthcheckup.ca website, and their food choices through the website of the Dieticians of Canada, eaTracker.ca, through the MyFitnessPal application, or on paper.

### Measures for Aims 2 and 3

Aim 2 of the study is to determine whether habits are formed faster (3 months), are stronger at program completion (12 months), and are maintained for a longer period of time after program completion (24 months) in the enriched as compared to the standard GLB. Aim 3 of the study is to determine at 3, 12, and 24 months following implementation whether the effectiveness of the enriched GLB is mediated by stronger habit formation. Habit formation will be assessed using the following indicators (see Table 1): (1) Adherence to self-monitoring in relation to: (a) weighing themselves, (b) fat grams consumed, (c) calories consumed, and (d) physical activity; (2) Degree to which behaviour change occurred will be measured by the (a) fat gram intake (as measured by the mean self-reported daily intake recorded through online or paper tracking over the course of the assessment week), and (b) calorie intake (as measured by the mean self-reported daily intake recorded through online or paper tracking); (3) Degree of habit strength will be assessed for (a) self-monitoring and (b) carrying out behaviors with the Self-Report Index of Habit Strength (SRHI) [47], with a focus on automaticity, which reflects the active ingredient of habits [47]. The SRHI is a 12-item measure that assesses empirically derived features of habits (e.g. degree of repetition, automaticity) on rating scales ranging from 1 (*disagree*) to 7 (*agree*). The SRHI has been shown to have high internal consistency (alpha = .89), test-retest reliability (*r* = .91), and divergent and convergent validity [22]. The scale was adapted for the purposes of this study and is available from the authors.

### Sample size

The primary outcomes are the differences in mean percentage weight loss between the enriched and standard GLB at 3, 12, and 24 months. The recent systematic review and meta-analysis by Ali et al. [19] of all GLB studies conducted so far allowed for calculating the mean % weight loss achieved in studies with follow-ups at 3 months (*N* = 11 studies) and at 12 months (*N* = 16 studies). Results showed a mean percent weight loss from baseline of 4.37% at 3 months and 4.35% at 12 months. Meta-analysis data for longer time frames are not available. The Finnish Diabetes Prevention Study, however, found a weight regain of around 33% at 2 years after completion of the intervention. Therefore, in the standard GLB, the expected percentage weight loss at 24 months (from baseline) is 2.92%. Based on the effect sizes in our preliminary data [23-25,34], we expect an additional weight loss of 3% at all three time points when if-then plans and mental practice are added to the program (possibly more at 24 months because we are expecting less weight regain). Based on a meta-analysis of past GLB studies [19], we expect the standard deviations for percent weight loss to be 4.3 in the enriched and standard GLB groups at the 3 time points. Using these inputs, a sample size of 64 participants per group is sufficient to estimate the between-group difference to an accuracy of ± 1.5% and a 95% CI at all 3 time points. To account for a potential drop out of around 20% (in line with comparable studies), we are increasing the sample size to *N* = 154, *n* = 77 per group.

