## Methods/Design

### Trial design

The McGill CHIP Healthy Weight Program is a randomized controlled trial (RCT) with a parallel group design. Participants will be randomly assigned (1:1) to either the enriched or the standard GLB. Primary and secondary outcome measures are completed at baseline, after 3 months (completion of the 12 weekly sessions, core program), after completion of the program (12 months), and one year after completion of the program (24 months).

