### Randomization

To randomize participants to the two intervention arms, a randomization sheet generated by a random digit generator is used (http://www.randomizer.org). Throughout the recruitment process, the list of randomized numbers will be assigned to participants by the research coordinator in sequential order from 1 to 154 in the order in which participants completes the baseline CHIP appointment. Once a participant is assigned a condition, the research coordinator enters the date and the participant’s initials next to the condition on the randomization sheet. This information together makes up the participant’s anonymous intervention code. Participants are told that the study evaluates two different approaches to lifestyle changes to see if one is superior to the other. Throughout the recruitment process, groups of approximately 6 to 10 people will be created according to their language (i.e., French or English), location, and time of day preferences. It was inherently not possible to blind the interventionist to interventions. However, the staff assessing the outcome variables (e.g. weight, EST) is blind to which intervention the participants were assigned.

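### The stated ±1.5% precision with 64 per group assumes independent participants, although both arms are treated in groups of about 6 to 10

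*Protocol article*

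**What the plan says.** The Sample size section justifies the trial by precision. It takes a common SD, "we expect the standard deviations for percent weight loss to be 4.3 in the enriched and standard GLB groups at the 3 time points", and concludes that "a sample size of 64 participants per group is sufficient to estimate the between-group difference". The full target is "to estimate the between-group difference to an accuracy of ± 1.5% and a 95% CI at all 3 time points". It then adds an allowance for attrition, "To account for a potential drop out of around 20% (in line with comparable studies), we are increasing the sample size to" 154, or 77 per arm. The expected benefit is stated separately: "we expect an additional weight loss of 3% at all three time points". No ICC, design effect or other allowance for group delivery is among the inputs.

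The design sections describe individual allocation followed by group treatment. Under Trial design, "Participants will be randomly assigned (1:1) to either the enriched or the standard GLB". Under Intervention, for a programme delivered over one year in either form, "Group sizes will comprise of approximately 6-10 individuals and the sessions will last for approximately one hour". Under Randomization, "groups of approximately 6 to 10 people will be created according to their language (i.e., French or English), location, and time of day preferences".

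**The concern.** Participants who attend the same sessions for a year influence one another and receive the same delivery of the programme. Their weight losses may therefore be correlated within a session group, even though each person was allocated individually. Where that happens, the variance of the difference between arms exceeds the independent-observations variance, and 64 people per arm carry less information than the calculation credits them with.

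What is at stake is the one quantitative promise on which the sample size rests. The article says the size is sufficient for a given accuracy; if group delivery induces even a small correlation, it is not. The calculation also leaves no slack to absorb this.

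**Working it through.** **Inputs from the protocol article.** SD 4.3 in both arms, target half-width 1.5, 95% CI, 64 per arm before dropout, 77 per arm randomised, about 20% dropout, expected difference 3 points (Sample size); groups of about 6 to 10 (Intervention, Randomization).

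**Assumed.** ICC 0.01 to 0.10, because the documents give none; mean group size m = 8, the middle of the stated range; the same ICC at all three time points.

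**Step 1: reproduce the stated figure.**
- n per arm = 2 × (1.96 × 4.3 / 1.5)² = 63.14, rounded up to 64.
- Half-width at 64 = 1.96 × 4.3 × √(2/64) = 1.49.

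The figure reproduces with a design effect of exactly 1, so no clustering allowance is hidden in it. The slack is 64/63.14 = 1.014.

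**Step 2: allow for group delivery.** Design effect DE = 1 + (m − 1) × ICC; half-width = 1.96 × 4.3 × √(2 × DE/64); analysed n needed for ±1.5 = 63.14 × DE, rounded up.

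| Assumed ICC | DE (m = 8) | Half-width, 64 analysed per arm | Analysed per arm needed for ±1.5 |
|---|---|---|---|
| 0 | 1.00 | ±1.49 | 64 |
| 0.01 | 1.07 | ±1.54 | 68 |
| 0.02 | 1.14 | ±1.59 | 72 |
| 0.05 | 1.35 | ±1.73 | 86 |
| 0.10 | 1.70 | ±1.94 | 108 |

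Across the stated group sizes (6 to 10), ICC 0.05 gives ±1.67 to ±1.79.

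**Step 3: break-even ICC.** (1.014 − 1)/(m − 1) gives about 0.003 for m = 6, 0.002 for m = 8 and 0.0015 for m = 10.

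**Step 4: precision at the planned N = 154.** After 20% loss, 77 × 0.8 = 61.6 are analysed per arm and 8 × 0.8 = 6.4 per group. There are 154/8 ≈ 19 groups (about 15 to 26 over sizes 10 to 6), hence about 17 degrees of freedom and a t quantile of 2.11. Half-width = 2.11 × 4.3 × √(2 × DE/61.6), with DE = 1 + 5.4 × ICC.

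| Assumed ICC | DE (m = 6.4) | Half-width, t on 17 df |
|---|---|---|
| 0 | 1.000 | ±1.63 |
| 0.02 | 1.108 | ±1.72 |
| 0.05 | 1.270 | ±1.84 |
| 0.10 | 1.540 | ±2.03 |

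The sources separate as follows. Analysing 61.6 instead of 64 moves ±1.49 to ±1.52. The t quantile moves it to ±1.63. Only the rest is due to the ICC. The first step arises because 64/0.8 = 80 would have to be randomised to retain 64, not 77; that is a separate point.

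**Step 5: power for 3 points.** With 64 analysed, m = 8 and the normal quantile, Φ(3/SE − 1.96) is 97.7% at ICC 0, 92% at 0.05 and 86% at 0.10; over m = 6 to 10 at ICC 0.10 it is 82 to 90%. On the basis of step 4, Φ(3/SE − 2.11) is about 91% at ICC 0.05 (SE 0.873) and 84% at 0.10 (SE 0.962).

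**Step 6: coverage, only if an analysis ignored groups.** 2Φ(1.96/√DE) − 1, with DE from step 2, is 94.2%, 93.4%, 90.8% and 86.7% at ICC 0.01, 0.02, 0.05 and 0.10.

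**The case against.** **The analysis may handle groups.** A reader might infer that the trial's 95% interval will under-cover and its type I error exceed 5%. The documents do not support that. The article states no model for the primary outcome, the analysis plan is not shown, and its absence is no finding. The figures in step 6 hold only if the analysis ignores groups. If it models them, coverage is kept and the cost is width. The precision statement is affected in either case.

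**Not all similarity within a group counts.** Groups are formed by language, location and time preference, but allocation is individual. Similarity that people bring with them is already in the individual SD and does not inflate the variance of the comparison; only correlation created by delivery does. The relevant ICC may therefore be smaller than the raw within-group correlation. The article also does not say that groups are closed to new members or that each keeps one coach, so neither can be used to argue for a large ICC. This stands.

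**The size rests on assumed values.** Also true. At ICC 0.01 the loss is only about 0.05 points, and one ICC for all three visits is a simplification, since the 24-month visit falls a year after the sessions end. But keeping ±1.5 needs an ICC close to zero, which the article neither states nor justifies.

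**Power is adequate.** A reader might conclude that the trial is too small to detect its expected effect. It is not: even ±2.03 around 3 points excludes zero. This lowers the severity, but does not rescue a sample size that was justified by precision.

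**Conclusion.** The point holds as a correction of the stated precision. The sentence that 64 per arm give ±1.5% with a 95% CI is correct only under independence, and the article's own description of group delivery in both arms gives no ground for assuming it. For groups of 8 the claim fails once the ICC exceeds about 0.002. Over an assumed ICC of 0.01 to 0.10 the half-width with 64 analysed is ±1.54 to ±1.94. At the planned N with 20% dropout and small-sample degrees of freedom it is about ±1.72 to ±2.03 for ICC 0.02 to 0.10, with clustering responsible only for the part above ±1.63.

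That the calculation makes no clustering allowance is certain; the size of the shortfall depends on the assumed ICC and group size. The documents support neither a claim that the final interval will be invalid nor a claim that the trial is underpowered for 3 points. Severity: should fix.

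**What to change.** - Keep N = 154.
- For the primary outcome, include session group as a random effect in both arms, with small-sample degrees of freedom (Satterthwaite or Kenward-Roger). If the analysis plan already does this, only the next change is needed.
- In the Sample size section, replace the ±1.5% claim with a figure computed on the same basis as that analysis, for example: about ±1.7 to ±2.0 for an assumed ICC of 0.02 to 0.10, groups of 8, 20% dropout (61.6 analysed per arm) and t on about 17 df. State that the ICC is assumed, and that ±1.63 would apply at ICC 0 because of the dropout shortfall and the degrees of freedom. Do not combine the normal quantile and 64 analysed with a small-sample analysis; that would understate the width.

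The cost is one model term and one revised sentence, with no extra participants and no change to the intervention. The stated precision becomes less favourable.

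### 77 per group keeps 64 evaluable only up to about 17% dropout, not the stated 20%, and the SD of 4.3 is an unsupported assumption at 24 months

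*Protocol article*

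**What the plan says.** All of this stands in one paragraph of the protocol article, under Sample size. The trial is sized on precision, with no power stated, for an outcome at three time points: "The primary outcomes are the differences in mean percentage weight loss between the enriched and standard GLB at 3, 12, and 24 months". Allocation is equal (Trial design: "Participants will be randomly assigned (1:1) to either the enriched or the standard GLB").

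The precision claim is that "a sample size of 64 participants per group is sufficient to estimate the between-group difference to an accuracy of ± 1.5" per cent, "and a 95% CI at all 3 time points". The dropout step follows: "To account for a potential drop out of around 20% (in line with comparable studies), we are increasing the sample size", to 77 per group and 154 in total. The inflation formula is not shown.

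The SD is introduced with "Based on a meta-analysis of past GLB studies [19" and continues: "we expect the standard deviations for percent weight loss to be 4.3 in the enriched and standard GLB groups at the 3 time points". A few sentences earlier the paragraph reports that this meta-analysis supplied mean weight loss at 3 months (11 studies) and 12 months (16 studies), and adds: "Meta-analysis data for longer time frames are not available". For the 24-month mean it turns to a different source, the Finnish diabetes prevention study. It names no other source for the 24-month SD.

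**The concern.** There are two separate points, and they differ in certainty and in size.

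The first is arithmetic. A dropout allowance is meant to leave the required number evaluable after the stated loss, so the required number is divided by the proportion retained. Multiplying by one plus the dropout rate gives too few. The stated 77 agrees with the multiplication and not with the division, so the randomized number and the stated dropout rate do not fit together.

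The second is the support for an input. The paragraph assigns one SD to all three time points on the strength of a source that, by its own account, stops at 12 months. The 24-month comparison is part of the primary outcome, and it is the one that tests whether weight loss lasts after the programme ends, which the Background gives as the reason for enriching it. A reader would take ±1.5 at 24 months to rest on the same evidence as at 3 and 12 months. It does not.

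**Working it through.** **Inputs.** From the Sample size section: SD 4.3 in both groups, target half-width 1.5 percentage points, 95% confidence, dropout about 20%, 77 per group randomized, expected difference 3 percentage points. Equal allocation is from Trial design. The SDs other than 4.3 used in step 5 are assumptions made for this check.

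**1. The plan's evaluable number.** Half-width = 1.96 × SD × √(2/n), so n = 2 × (1.96 × SD / half-width)².
- n = 2 × (1.96 × 4.3 / 1.5)² = 63.1, rounded up to 64. This reproduces the plan.
- At n = 64 the half-width is 1.96 × 4.3 × √(2/64) = 1.490 (1.504 with a t quantile).

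**2. The dropout step.**
- 64 × 1.2 = 76.8, rounded up to 77; 2 × 77 = 154. This reproduces the plan.
- 64 / 0.8 = 80; 2 × 80 = 160. This does not.
- Shortfall: 3 per group, 6 in total.
- Dropout at which 77 still leaves 64: 1 − 64/77 = 16.9%.

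**3. Precision with 154 randomized and 20% lost.**
- Remaining per group: 77 × 0.8 = 61.6.
- Half-width: 1.96 × 4.3 × √(2/61.6) = 1.519 (1.534 with t).
- This is 0.03 wider than the 1.490 at 64 per group and 0.02 above the stated 1.5.
- The largest SD that still meets ±1.5 at 61.6 per group is 1.5 / (1.96 × √(2/61.6)) = 4.25, just under the planned 4.3.

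**4. Practical effect.** For the expected difference of 3 points, 3 / (4.3 × √(2/61.6)) = 3.87. Subtracting 1.96 leaves 1.91, so two-sided 5% power is about 97%.

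**5. 24-month precision under assumed SDs, 61.6 per group.** The half-width is 1.96 × SD × 0.1802.

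| Assumed SD at 24 months | Half-width |
|---|---|
| 3.0 | ±1.06 |
| 4.0 | ±1.41 |
| 4.3 (plan) | ±1.52 |
| 5.0 | ±1.77 |
| 6.0 | ±2.12 |

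The direction is open. If every participant regained 33% of the weight lost, the proportion the paragraph uses for its 24-month mean, the SD would shrink to 0.67 × 4.3 = 2.9 and the half-width would be about ±1.0. If regain varied widely between participants, the SD could exceed 4.3. The document has no figure that decides between these.

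**The case against.** The strongest defence of the dropout step is that everything is stated loosely and the effect is tiny. The target is given to one decimal, and 1.519 still rounds to 1.5. The dropout is approximate, and 17% may fall within it. With a t quantile, even the planned 64 per group gives 1.504, so the miss is of the same order as the choice between z and t. The multiplication by 1.2 is inferred. All of this stands as to size. It does not remove the mismatch: the allowance is there to leave 64 after the stated loss, and at 20% it leaves 61.6.

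On the SD, the defence is that the sentence states a planning expectation. It does not say that the meta-analysis reports a 24-month SD, and the absence of longer data is openly disclosed. Carrying one SD forward is a common assumption. That also stands, and it makes the value unsupported rather than wrong. But the sentence bases the figure for all three time points on the meta-analysis, and nothing marks the 24-month value as an extrapolation.

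A reader might go further and infer that 154 participants cannot deliver the planned precision, or that variable regain can only widen the 24-month SD, so that the claim there fails by a wide margin. The document supports neither inference. The dropout slip costs 0.03 points, and proportional regain would narrow the SD. A sensitivity range that ran only upward from 4.3 would put unsourced values in place of an unsourced value.

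**Conclusion.** Both points hold, at modest size.

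The stated 77 per group does not match the stated 20% dropout. It covers about 17%; at 20% the half-width is about ±1.52 (±1.53 with t) instead of ±1.5. This rests only on the plan's own inputs. Power for the expected 3 points stays near 97%, so it is a correction to a stated figure and not a threat to the trial.

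The 24-month SD of 4.3 has no support in the source it is credited to. Precision at 24 months is therefore unsupported, which is different from being shown to fail: depending on the SD assumed, it could be better or worse than ±1.5. The two points should be kept apart, since the certain one is small and the possibly larger one cannot be sized from the document.

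**What to change.** Keep N = 154 and change the text of the Sample size section:

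- Restate 77 per group as allowing for about 17% dropout or, equivalently, as giving about ±1.52 if 20% drop out. Going to 80 per group (160) would also reconcile the figures, but a gain of 0.03 points does not require it.
- Limit the attribution of SD 4.3 to the meta-analysis to 3 and 12 months, and label the 24-month SD as an assumption.
- Take 24 months out of the single ±1.5 claim and give its precision over a two-sided assumed range. For example, at 61.6 per group, SDs of 3.0 to 6.0 give about ±1.06 to ±2.12, with the SDs marked as assumed.

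The cost is a few sentences and a slightly less favourable stated precision. Conduct, recruitment and budget are unaffected.
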